# Protocol summary

Title: Safety and efficacy of methylene blue combined with artesunate or amodiaquine for malaria treatment in children of Burkina Faso: a pilot study in the frame of the A8 Project of the SFB 544

Design: Single-centre, randomized controlled study in children with uncomplicated falciparum malaria in the Nouna Health District, north-western Burkina Faso

Phase: Phase II

Objectives: The primary objective of this trial is to study the safety of the combination methylene blue (MB)-artesunate (AS) and MB-amodiaquine (AQ) given over three days in 3-4 years old children with uncomplicated falciparum malaria in an area of high malaria transmission intensity compared to the safety of a three days AS-AQ regimen. Secondary objectives are to investigate the efficacy of MB-AS and MB-AQ.

Population: Children aged 3-4 years with uncomplicated malaria from Nouna town.

Sample size: N= 180 (n=60 for each group).

Treatment: The participants in the MB-AS group will receive orally twice daily 10mg/kg MB combined with once daily 4mg/kg AS over 3 days. The participants in the MB-AQ group will receive orally twice daily 10mg/kg MB combined with once daily 10mg/kg AQ over 3 days. The participants of the comparator group will receive a 3 day regimen of once daily oral AS (4mg/kg) combined with once daily AQ (10mg/kg).

Endpoints: The primary endpoint is the number of adverse events (AE) after drug intake until day 28. Secondary endpoints are the number of serious adverse events (SAE), adequate clinical and parasitological response (ACPR) rate on day 28, clinical and parasitological failure rates on day 3, 7, 14 and 28, changes in haemoglobin/haematocrit until day 28, and fever and parasite clearance time.

Study duration and dates: The study will be implemented during the rainy season of the year 2006 (July - October).

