# Design of the trial

Single-centre, randomized, controlled phase II trial in children aged 3-4 years with uncomplicated falciparum malaria.

Randomisation and blinding

After creation of computer generated envelopes, 180 children aged 3-4 years with uncomplicated falciparum malaria will be randomized to one of the three treatment groups: MB-AS (3 day regimen), MB-AQ (3 day regimen), AS-AQ (3 day regimen).

Due to the coloration of urine through MB, blinding of patients will not be possible. However, all lab technicians examining the blood samples for malaria parasites and other study relevant aspects will be blinded to treatment regimen.

Duration of the trial

The study will become implemented between July and October 2006.

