# Treatment of subjects and clinical study procedures

Description of the treatments

All patients in the MB-AS group will receive for 3 days twice daily (morning and evening) 10mg/kg MB accompanied by once daily (morning) 4mg/kg artesunate (= 4mg/kg total daily dose).

MB will be given according to the following weight table:

10,0 – 16,0 kg = 130mg = 2 tablets per treatment = 2 x 2 tablets /day

16,5 – 22,5 kg = 195mg = 3 tablets per treatment = 2 x 3 tablets/ day

AS will be given according to the following weight table:

10,0 – 16,0 kg = 50mg = 1 tablet per treatment = 1 tablet per day

16,5 – 22.5 kg = 100mg = 2 tablets per treatment = 2 tablets per day

AQ will be given according to the following weight table:

10,0 – 16,0 kg = 100mg = 1 tablet per treatment = 1 tablet per day

16,5 – 22.5 kg = 200mg = 2 tablets per treatment = 2 tablets per day

Product description

MB (Urolene Blue®, Star Pharmaceuticals, USA); 1 tablet Urolene Blue® = 65mg)

AS (Artesunate®, Guilin Pharmaceuticals Co., Ltd., China; 1 tablet Artesunate® = 50mg)

AQ (taken from the essential drug store of the Ministry of Health, Burkina Faso; 1 tablet amodiaquine=100mg)

Concomitant treatments

Patients having received antimalarial treatment prior to inclusion (last three days) will be excluded except children having been treated with chloroquine.

All children having fever ≥ 38.5°C will receive standard doses of paracetamol (= acetaminophen; 10 mg/kg) until symptoms subside (taken from the essential drug stock of the Ministry of Health, product description: paracetamol tablets or syrup).

All indicated drugs are allowed, except other western antimalaria drugs, antibiotics with antimalarial efficacy, acetanilide and phenacetin, nalidixic acid, niridazole, nitrofurantoins and sulphonamides (or any other drug that might induce haemolysis in G6PD deficient individuals) from beginning of treatment until end of follow-up.

Prior and concomitant illnesses

History of prior illnesses will become investigated and recorded. All relevant concomitant illnesses will be recorded based on the examination of the study physicians at D0, D1, D2, D3, D7, D14 and D28.

Procedures for monitoring subject compliance

Drug intake will be directly monitored by a study nurse or a field worker for the whole treatment period, supervised by the study physicians.

Visits and treatment schedule

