After identification of febrile children in the specified age group in the community, enrolled children are treated and supervised as outpatients according to the study flow explained in chapter 3. Children are examined at regular intervals (D0, D1, D2, D3, D7, D14 and D28) by a study physician. In case of not coming to the clinic on respective examination days, children will be visited at home by field staff. Parents/guardians are instructed to return to the hospital in case of worsening of their child’s clinical condition at any time during the follow-up period.

Day 0

- Presentation of the febrile child at one of the fever measurement points
- Informed consent
- Baseline status (weight, temperature)
- Examination 1 (at the Nouna district hospital)
- Questioning for inclusion/exclusion criteria
- Capillary blood sample for a thin and thick blood film (malaria) and haematocrit
- 1 filter paper is kept for genotypic determination of G6PD deficiency
- 1 filter paper is kept to distinguish between recrudescence and reinfection according to PCR during follow-up
- Treatment 1 (before 14:00) – MB-AS or MB-AQ or AS-MB
- Treatment 2 (evening) – MB

Day 1

- Examination 2 (morning)
- Treatment 3 (morning) – MB-AS or MB-AQ or AS-MB
- Treatment 4 (evening) – MB

Day 2

- Examination 3 (morning)
- Capillary blood sample (parasitemia and haematocrit)
- Treatment 5 (morning) – MB-AS or MB-AQ or AS-MB
- Treatment 6 (evening) – MB

Day 3

- Examination 4 (morning)
- Capillary blood sample (parasitemia and haematocrit) (morning)

Day 7, 14 and 28

- Examination 5, 6 and 7 respectively (morning)
- Capillary blood sample for parasitemia and haematocrit

Other time periods

- Phaenotypical G6PD determination and further investigations according to study physicians judgement will take place at any day between D0 and D28 in case of haemolysis
- 1 filter paper is kept to distinguish between recrudescence and reinfection according to PCR during follow-up (D7, 14, 28 and any other day the child returns for examination between D3 and D28)

Clinical management of (serious) adverse events

Study physicians and emergency medications will be available 24h to deal with SAEs. Additional laboratory tests are available 24h if needed and a standard blood transfusion service is established at the hospital (e.g. in case of haemolysis).

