# Assessment of primary endpoint

Specification of parameter

- Number and proportion of patients with at least one observed or self-reported adverse event (definition below)

Methods of data collection

Data on the occurrence of adverse events (severity, seriousness, causality), concomitant illnesses and concomitant drugs will be collected through direct continuous active clinical surveillance (including laboratory results) of all study subjects. All children will be examined by the responsible study physician at D0, D1, D2, D3, D7, D14 and D28.

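### Watched evening MB doses give both MB arms three staff contacts that AS-AQ lacks, so the opportunity to record the open-label primary AE endpoint is unequal and nothing equalises it

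*Protocol*

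**What the plan says.** **Dosing.** Under Treatment of subjects and clinical study procedures, the MB-AS group "will receive for 3 days twice daily (morning and evening) 10mg/kg MB accompanied by once daily (morning) 4mg/kg artesunate". The Protocol summary gives the MB-AQ group "orally twice daily 10mg/kg MB combined with once daily 10mg/kg AQ over 3 days". It gives the comparator "a 3 day regimen of once daily oral AS (4mg/kg) combined with once daily AQ (10mg/kg".

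**Schedule.** The visit list has an evening item on each of D0, D1 and D2 (Treatments 2, 4 and 6). Each contains MB alone, for example "Treatment 2 (evening) – MB". No placebo and no evening visit is listed for AS-AQ.

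**Observation of doses.** "Drug intake will be directly monitored by a study nurse or a field worker for the whole treatment period". The children are outpatients.

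**Primary endpoint.** Assessment of primary endpoint specifies "Number and proportion of patients with at least one observed or self-reported adverse event". AEs are to be collected by active and continuous surveillance of all children, with physician examinations on the same seven days in every arm.

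**Blinding.** Design of the trial says that patients cannot be blinded because MB colours the urine. The only staff stated to be blinded are in the laboratory: "all lab technicians examining the blood samples for malaria parasites and other study relevant aspects will be blinded to treatment regimen".

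**The concern.** The number of staff contacts in the acute phase is tied to the randomised arm. The endpoint is binary, so a single mild event that a nurse sees, or that a guardian mentions at an evening dose, turns a child into a case. The person giving that dose knows that the child is on MB. An AS-AQ child has no contact at that hour.

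The Statistics section plans a global chi-square test of the three arms and then three pairwise tests. Two of the three pairs set an MB arm against AS-AQ, and the trial objectives rely on that comparison to judge the safety of the MB combinations. Extra recording in the MB arms could produce an apparent safety signal where there is none. It could also hide better tolerability of MB-AS, which is the difference that the Statistics section assumes.

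**Working it through.** **1. Contact count** (from the dosing text and visit list; a morning dose and a same-day examination count as one contact)

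| Period | Each MB arm | AS-AQ |
|---|---|---|
| D0-D2 mornings | 3 | 3 |
| D0-D2 evenings | 3 | 0 |
| D3, D7, D14, D28 | 4 | 4 |
| Total | 10 | 7 |

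The whole difference is the three evenings. MB-AS and MB-AQ have identical counts.

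The count takes the third arm as AS-AQ, as the Protocol summary, flow chart, Design of the trial and Statistics all do. The visit list prints the third regimen as AS-MB and does not restrict the evening item to the MB arms. Those places must be reconciled.

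**2. The plan's own figure.** Statistics assumes AE rates of 25% (AS-AQ), 25% (MB-AQ) and 5% (MB-AS).
- Mean = (0.25 + 0.25 + 0.05)/3 = 0.1833. Variance = (2 × 0.0667² + 0.1333²)/3 = 0.0089.
- Noncentrality = n × 3 × variance/[mean × (1 − mean)], 2 df, 5% level.
- n = 54 with exact rates: 9.62, power 0.799. With the printed 0.009 and 0.183: 9.75, power 0.805. The stated 54 per group for 80% power is reproduced.
- n = 60, the number to be enrolled: 10.69, power 0.842. For the pair 25% against 5%, power is 0.876.

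**3. Illustration of size.** Let p be the AE rate recorded through the contacts that all arms share. Let q be the chance that one evening contact brings to light a first AE in a child with none recorded. The documents give no value for q; 0-3% is an assumption.

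Recorded MB rate = 1 − (1 − p)(1 − q)³. AS-AQ stays at p.

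No true difference, p = 25%, 60 per arm:

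| q | Recorded MB rate | Excess over AS-AQ | Global test rejects |
|---|---|---|---|
| 0 | 25.0% | 0 | 5% |
| 1% | 27.2% | 2.2 points | about 6% |
| 2% | 29.4% | 4.4 points | about 8% |
| 3% | 31.5% | 6.5 points | about 12% |

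For q = 3%: 1 − 0.75 × 0.97³ = 0.3155; noncentrality = 60 × 0.00286/(0.2937 × 0.7063) = 0.83; rejection probability 0.117. Simulation with 200,000 runs gave 0.118.

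Planned scenario (25/25/5%), 60 per arm:

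| q | Recorded MB-AS rate | Power, MB-AS v AS-AQ |
|---|---|---|
| 0 | 5.0% | 0.876 |
| 1% | 7.8% | 0.725 |
| 2% | 10.6% | 0.542 |
| 3% | 13.3% | 0.369 |

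The lower rows are demanding. At q = 3% the evenings would have to reveal 8.3 points of extra cases on top of 5 points recorded otherwise. The table shows sensitivity and is not a forecast.

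**4. How far the assumptions carry the answer.** A different model gives excess = (any-AE rate) × (share of events starting on D0-D2) × (detection with evenings − detection without). Assume a rate of 25-40%, an early share of 50-80%, detection of 75-90% with evening contacts and 50-70% without. The smallest value is 0.25 × 0.5 × (0.75 − 0.70) = 0.6 points. The largest is 0.40 × 0.8 × (0.90 − 0.50) = 12.8 points. If detection is equal, the excess is zero. The inputs are again assumed, so the documents do not fix the size.

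**The case against.** A reader might infer that AEs are actively looked for more often in the MB arms, or that an evening event can reach staff only in those arms. The documents support neither.

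- The sentence on watched intake stands under compliance monitoring. No text assigns AE questioning to the nurse or field worker at the evening dose, and the AE form is signed by the attending physician.
- Surveillance is described identically for all children, and the physician examinations fall on the same days in every arm.
- The evenings of D0, D1 and D2 are each followed by a morning examination (Examinations 2, 3 and 4). An AS-AQ guardian can report the night's event there, and self-reports count. Guardians of all children are also told to come back if the child gets worse.
- Some evening events in the MB arms are real effects of a real extra dose, and counting them is correct.
- How AEs are elicited may be settled in forms, working instructions or a statistical analysis plan that is not shown.

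Most of this stands, and it narrows the point to events that are brief or not recalled by morning. It does not remove it. The protocol itself fixes the unequal contacts, counts observed events, and does not limit AE collection to the common examinations. Calling surveillance continuous does not give an AS-AQ outpatient an evening contact.

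**Conclusion.** The point holds as unequal opportunity for AE ascertainment: 6 against 3 dosing contacts on D0-D2 and 10 against 7 contacts overall, with an unblinded any-AE endpoint and no provision to equalise. The likely direction is against MB in the MB-AS v AS-AQ and MB-AQ v AS-AQ comparisons. MB-AS v MB-AQ is untouched.

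The size is unknown and may be zero. Under the assumed 0-3% extra detection per evening contact and a 25% rate with no true difference, the recorded MB rate would be 25-31.5% and the global 5% test would reject in about 5-12% of trials. The stronger statement, that the primary result is biased by a known number of points, is not supported, because every detection rate used here is an assumption. The sample size needs no change on this account. The point merits a change to the protocol because the remedy is cheap and because the planned MB-AS v AS-AQ contrast is sensitive to small differences in detection.

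**What to change.** 1. In Assessment of primary endpoint, state that AEs are elicited in all arms with the same question at the six common post-dose examinations (D1, D2, D3, D7, D14, D28). The question should cover the time since the previous scheduled examination (on D1, since the first dose), so that the recall window is equal. The D0 examination precedes the first dose and does not count.
2. On the AE form, record the contact at which the event was first found (common examination, evening dose, unscheduled return) and whether it was reported again at the next common examination.
3. Keep all AEs that the endpoint covers in the safety analysis, including those found at evening doses or unscheduled returns. Removing them could hide genuine effects of the evening MB dose.
4. Pre-specify a further comparison of AE proportions that leaves out AEs found only at evening dosing contacts, and read any MB v AS-AQ difference in the light of both analyses.

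**Cost.** A small addition to the AE form and one extra analysis; no added visits, staff or children. The restricted comparison may miss some real but short-lived effects of the evening dose, so it accompanies the all-AE analysis and does not replace it. An event that staff witnessed in the evening is more likely to be repeated next morning, so the restriction reduces and exposes the imbalance but may not remove it.

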**Examination 3**

3 days regimen MB-AS or MB-AQ or AS-AQ

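### The day-by-day schedule lists MB-AS twice, never names the AS-AQ comparator, and leaves open which arms the evening MB entries apply to

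*Protocol*

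**What the plan says.** Under Treatment of subjects and clinical study procedures, the part on visits and treatment schedule lists six treatments over Days 0 to 2.

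- Morning entries, each offering "MB-AS or MB-AQ or AS-MB": "Treatment 1 (before 14:00) – MB-AS or MB-AQ or AS-MB", "Treatment 3 (morning) – MB-AS or MB-AQ or AS-MB" and "Treatment 5 (morning) – MB-AS or MB-AQ or AS-MB".
- Evening entries: Day 0 reads "Treatment 2 (evening) – MB". Treatments 4 and 6 follow the same pattern on Days 1 and 2. None names an arm.

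Other parts of the protocol describe the third arm differently.

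- Protocol summary: "The participants of the comparator group will receive a 3 day regimen of once daily oral AS (4mg/kg) combined with once daily AQ (10mg/kg" (per dose, over the three days). MB is not part of that regimen.
- Flow chart label: "3 days regimen MB-AS or MB-AQ or AS-AQ".
- Trial objectives and Design of the trial (randomisation): the third group is AS-AQ.
- Statistics, sample size calculation: the planning rates include an AQ+AS group.
- Definitions, adverse events: blue urine is expected in the MB-AS and MB-AQ groups only.

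The description of the treatments, in the same section as the schedule, opens with "All patients in the MB-AS group will receive for 3 days twice daily (morning and evening) 10mg/kg MB" and adds the AS component of that arm. It then gives weight tables for MB, AS and AQ, without a sentence on what the MB-AQ or AS-AQ arm receives.

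**The concern.** The schedule is operative text: it says what is given at each treatment time. AS-MB and MB-AS are the same pair of drugs, so a child randomised to AS-AQ matches no morning entry. If the third label is taken to stand for the comparator, it points to MB in place of AQ. The evening entries, having no arm attached, can be read as applying to every child.

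Two things are at stake. One is exposure of comparator children to a drug they were not assigned. The other is the reference group: the stated purpose of AS-AQ is to help judge the safety of the two MB combinations, and the primary endpoint is adverse events. Blinding is described only for laboratory technicians, so it does not stop dosing staff from working by arm label, and a wrong label in the schedule could reach the child.

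**Working it through.** The check is a comparison of passages, plus a count and one piece of arithmetic on the protocol's planning rates.

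**1. Count of schedule entries.**

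| Entries | Number | Name AS-AQ | Carry the AS-MB label | List MB with no arm |
|---|---|---|---|---|
| Morning (Treatments 1, 3, 5) | 3 | 0 | 3 | – |
| Evening (Treatments 2, 4, 6) | 3 | 0 | – | 3 |

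**2. What a comparator child would receive, by source.** The literal reading takes the third morning label as the comparator and the evening entries as applying to all arms.

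| Drug | Protocol summary | Schedule, read literally |
|---|---|---|
| AS | 3 treatment times | 3 treatment times |
| AQ | 3 treatment times | 0 |
| MB | 0 | 3 morning + 3 evening = 6 |

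**3. Is it a text-extraction fault?** Unlikely. The same label appears on three separate days in plain list text, while the flow chart label in the same document prints AS-AQ.

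**4. Does the treatment description resolve it?** Only in part. Its AS and AQ tables give tablets per day, and the MB table gives two administrations per day. A reader who already knows the arm can work out daily tablets. The section does not say which tables apply to which arm, and the narrative sentence covers MB-AS alone. MB-AQ lacks a sentence as well, so the gap is not special to the comparator.

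**5. Which way would contamination bias the comparisons?** The Statistics section assumes adverse event rates of 25% for AQ+AS, 25% for AQ+MB and 5% for AS+MB. Suppose a fraction f of comparator children received AS+MB instead. The comparator rate becomes 25 − 20f percent, so:

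- contrast with MB-AS: (25 − 20f) − 5 = 20(1 − f) points, from 20 at f = 0 to 0 at f = 1;
- contrast with MB-AQ: 25 − (25 − 20f) = 20f points, from 0 at f = 0 to 20 at f = 1.

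One contrast shrinks and the other grows. If MB were instead added to AS-AQ in the evenings only, the relevant rate is that of all three drugs together. The protocol gives none, so the direction is unknown.

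**The case against.** The strongest reply is that this is a drafting slip that any reader of the whole protocol would see through. AS-AQ is named as the third arm in the summary, flow chart label, objectives, randomisation text and, as AQ+AS, the sample size text. The schedule itself sends the reader to the study flow in chapter 3, apparently the flow chart. Children are randomised by envelope to a group called AS-AQ, and a child so assigned fits no line of the schedule. That is at least as likely to prompt a question as to lead to silent misdosing. Nor does the protocol say which page or working sheet staff dose from.

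This stands as far as the likely consequence goes. It does not remove the contradiction, which is in dosing text and repeated on every treatment day.

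Four stronger readings are tempting, and the protocol does not support them.

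- A reader might infer that evening MB for comparator children is positively instructed. The entries can equally be read as the evening dose for children whose regimen contains MB, so this is an ambiguity.
- A reader might infer that the whole treatment section is silent on the comparator's drugs. The AS and AQ weight tables are there; what is missing is the link from arm to drugs.
- A reader might infer that all 60 comparator children would be misdosed. That requires staff to disregard every other statement of the arm, so it is a literal worst case.
- A reader might infer that contamination would pull the adverse event contrasts toward zero, or would spoil two designated primary comparisons. The planning rates contradict the first. On the second, the Statistics section sets out a global test and three pairwise tests and singles out no two as primary.

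**Conclusion.** The point holds as an internal inconsistency in the protocol. All three morning entries duplicate one MB arm and omit the comparator that the rest of the protocol defines. All three evening entries fail to say which arms they cover, and the treatment description does not close the gap.

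Read literally, the schedule leaves out the comparator and could expose up to 60 comparator children to unassigned MB; the 60 is the planned arm size, an upper limit and not an expected number. Contamination would bias the safety comparisons in a direction that cannot be stated in general. On the protocol's own planning rates, complete substitution would change each of the two contrasts involving the comparator by 20 points, one downward and one upward.

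This rests on two assumptions: that the schedule is used as an instruction, and that the printed text matches the source document. The sample size and power statements are unaffected. Whether the flow chart separates the arms cannot be judged from the text available, and nothing here depends on it.

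**What to change.** Before any child is treated, reconcile the schedule entries for Treatments 1 to 6 with the arm definitions in the Protocol summary, the flow chart label and Design of the trial. Replace the shared lines with a small table by arm, giving the morning and evening contents for each of Days 0, 1 and 2 and marking explicitly any treatment time at which an arm receives nothing. In the description of the treatments, add a statement of which drugs each of the three arms receives, so that the weight tables can be linked to arms. The clinical team must confirm the intended content of every entry; this review does not propose it.

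The cost is six schedule lines and one paragraph, with an amendment signed by the principal investigators and submitted to the two ethics committees, as the protocol already provides. Any dosing sheets prepared from the schedule should be checked at the same time. Sample size and analysis are unchanged.
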